### **11.2. Description of analysis sets for the step 2 (Simon's phase II trial)**

#### **11.2.1. Safety analysis set**

Safety and pharmacokinetic analyses will be performed on the safety-evaluable population. The safety-evaluable population is defined as all subjects treated with at least one dose of investigational product. Subjects who are not treated with any investigational product will be identified and described separately from the safety-evaluable population.

Erroneously treated patients will be accounted in the group for the treatment they actually received.

#### **11.2.2. Efficacy analysis set**

Efficacy analyses will be performed in modified intent-to-treat population (ITT) population ie, all patients following the major inclusion criteria and with a 3 months evaluation. Analyses will be repeated in the intent to treat principle i.e including all randomized patients whatever eligibility criteria and treatment received patients and in the per protocol population (patients who had received all the planned doses).

### **11.3. Methods of statistical analyses**

Continuous variables will be summarized using descriptive statistics, i.e. number of subjects with available data (N), mean, median, standard deviation (S.D.), 25% - 75% quartiles (Q1-Q3) and range. Continuous variables could be transformed as categorical variable using median or using conventional cut-off from bibliography or clinical practice. If required comparison using Chi square (or exact Fisher test) or Student T test (or Wilcoxon Mann and Whitney) tests will be done.

Categorical variables will be described by and percentages. The number of missing data will be described.

#### **Phase I**

Safety analyses will be performed on the first 9 patients. Toxicities during the first 2 cycles will be considered. If the same grade 3-4 adverse event is reported for more than 3 patient over 9, the trial could prematurely stop after reunion of the independent committee.

Data on safety will be completed during the second part of the study.

## **Phase II**

### **11.3.1. Safety Analyses**

#### **Analysis of safety endpoint(s)**

\* Safety analyses will be performed on the safety-evaluable population, defined as all subjects treated with at least one dose of investigational product.

\* Toxicities and grades will be described at each cycle.

\* The following data will be given:

- The number and percentage of patients with at least one adverse event
- The number and percentage of patients with at least one grade 3 or 4 adverse event
- The number and percentage of patients with at least one serious adverse event
- The number and percentage of patients with at least one adverse event leading to treatment premature stop
- Time until grade 3-4 toxicity will be determined using the Kaplan Meier method. Patients without toxicities will be censored.

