## **5.2.2 Duration of treatment and criteria for retreatment**

**Treatment will be delivered with a maximum of 24 months:**

- 4 months with the association Durvalumab + Tremelimumab + FOLFOX (M1 to M4)
- 20 months of maintenance with Durvalumab alone (M5 to M24)

Retreatment is allowed (**once only**) for patients meeting the retreatment criteria below. The same treatment guidelines followed during the initial 24-month (4 months with the association + 20 months maintenance) treatment period will be followed during the retreatment period, including the same dose and frequency of treatments and the same schedule of assessments.

Patients may undergo retreatment in 1 clinical scenarios, described below:

1. Patients who complete the 4 dosing cycles of the combination of durvalumab and tremelimumab portion of the regimen (with clinical benefit per Investigator judgment), but subsequently have evidence of PD during the durvalumab monotherapy portion of the combination regimen, with or without confirmation according to RECIST 1.1, may restart treatment with the combination (FOLFOX + Durvalumab + Tremelimumab).

Before restarting their assigned treatment, the Investigator should ensure that the patient :

- does not have any significant, unacceptable, or irreversible toxicities that indicate continuing treatment will not further benefit the patient.
- Still fulfils the eligibility criteria for this study, to restart folfox, durvalumab and tremelimumab.
- Has not received an intervening systemic anticancer therapy after their assigned treatment discontinuation.
- Has to perform a baseline tumor assessment within 28 days of restarting their assigned treatment; all further scans should occur with the same frequency as during the initial 12 months of treatment (relative to the date of randomization) until study treatment is stopped (maximum of 12 months of further treatment).

During the retreatment period, patients receiving durvalumab + tremelimumab may resume durvalumab dosing at 750mg q2w with 75 mg of tremelimumab q4w for 4 doses each and combined to FOLFOX for 3 months. Patients will then continue with durvalumab monotherapy at 750 mg q2w, until month 24 if no PD is observed.

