## **9. DISEASE EVALUATION AND METHODS**

The response to immunotherapy may differ from the typical responses observed with cytotoxic chemotherapy including the following (Wolchok et al 2009, Nishino et al 2013):

- Response to immunotherapy may be delayed
- Response to immunotherapy may occur after PD by conventional criteria
- The appearance of new lesions may not represent PD with immunotherapy
- SD while on immunotherapy may be durable and represent clinical benefit.

Based on the above-described unique response to immunotherapy and based on guidelines from regulatory agencies, e.g., European Medicines Agency's "Guideline on the evaluation of anti-cancer medicinal products in man" (EMA/CHMP/205/95/Rev.4) for immune modulating anti-cancer compounds, the study may wish to implement the following in addition to standard RECIST 1.1 criteria:

- RECIST will be modified so that PD must be confirmed at the next scheduled visit, preferably, and no earlier than 4 weeks after the initial assessment of PD in the absence of clinically significant deterioration. Treatment with durvalumab + tremelimumab would continue between the initial assessment of progression and confirmation for progression.
- In addition, subjects may continue to receive durvalumab + tremelimumab beyond confirmed PD in the absence of clinically significant deterioration and if investigators consider that subjects continue to receive benefit from treatment.

Modification of RECIST as described may discourage the early discontinuation of durvalumab + tremelimumab and provide a more complete evaluation of its anti-tumor activity than would be seen with conventional response criteria. Nonetheless, the efficacy analysis will be conducted by programmatically deriving each efficacy endpoint based on RECIST 1.1 criteria.

Of note, clinically significant deterioration is considered to be a rapid tumor progression that necessitates treatment with anti-cancer therapy other than durvalumab + tremelimumab or with symptomatic progression that requires urgent medical intervention (e.g., central nervous system metastasis, respiratory failure due to tumor compression, spinal cord compression).>>

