#### **10.2.1. Study recording period and follow-up for adverse events and serious adverse events**

Adverse events and serious adverse events will be recorded from time of signature of informed consent, throughout the treatment period and including the follow-up period (90 days after the last dose of durvalumab + tremelimumab or until the initiation of alternative anticancer therapy).

During the course of the study all AEs and SAEs should be proactively followed up for each subject. Every effort should be made to obtain a resolution for all events, even if the events continue after discontinuation/study completion.

If a subject discontinues from treatment for reasons other than disease progression, and therefore continues to have tumor assessments, drug or procedure-related SAEs must be captured until the patient is considered to have confirmed PD and will have no further tumor assessments.

The investigator is responsible for following all SAEs until resolution, until the subject returns to baseline status, or until the condition has stabilized with the expectation that it will remain chronic, even if this extends beyond study participation.

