#### **11.4. Determination of sample size**

**Step 1:** Nine patients will be included in the **safety** analyses. If the same grade 3-4 adverse event is reported for more than 1 patient over 3, the trial could prematurely stop after reunion of the independent committee. Patients from the safety population will be included in the efficacy set.

**Step 2:** The **efficacy** will be determined using a Simon 2 steps phase II design.

The hypotheses are the following:

The primary objective will be evaluated among MSS patients

A PFS of 3 months is not considered of interest. A PFS of 6 months is expected. This is equivalent to assume that a PFS of 50% at 3 months is insufficient and a PFS of 70.7% is expected. With  $\alpha=10\%$ ,  $\beta=10\%$  (90% power), 20% of non-evaluable patients, 52 patients with MSS disease are needed including patients of the safety population (9 patients)

The prevalence of MSS disease is around 90%-95%, thus 5 additional patients will be included

Overall the study will include 57 patients.

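### The Kaplan-Meier curve for time to grade 3-4 toxicity censors patients who die or start another anticancer therapy, so read as an absolute risk it is too high and will not match the crude percentage in the same list

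*Protocol*

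**What the plan says.** Section 11.3.1 analyses the safety-evaluable population, "defined as all subjects treated with at least one dose of investigational product". Among the listed outputs is "The number and percentage of patients with at least one grade 3 or 4 adverse event". The list ends with the time-to-event summary: "Time until grade 3-4 toxicity will be determined using the Kaplan Meier method. Patients without toxicities will be censored". So the protocol itself fixes both the estimator and who is censored. It names no competing event.

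Three other places decide how a patient leaves observation:

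- Section 10.2.1 runs AE recording from consent to "90 days after the last dose of durvalumab + tremelimumab or until the initiation of alternative anticancer therapy".
- Section 9 says that "subjects may continue to receive durvalumab + tremelimumab beyond confirmed PD in the absence of clinically significant deterioration", if the investigator sees continuing benefit. Section 5.2.2 lets patients who progress on maintenance restart the combination once.
- Section 5.2.2 also sets the length of exposure: "Treatment will be delivered with a maximum of 24 months".

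Section 10.1.5 makes a fatal event grade 5, which lies outside grade 3-4.

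**The concern.** Kaplan-Meier treats a censored patient as someone who could still have the event and would do so at the same rate as those still followed. That is not true of a patient who has died. It is also not a useful assumption for a patient whose recording was closed by a new anticancer therapy, since later events would not be recorded. Once such patients are censored, one minus Kaplan-Meier describes the risk in a setting where nobody dies or changes therapy. It no longer gives the share of treated patients who have grade 3-4 toxicity.

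Section 6.2.3 notes that this combination has not been evaluated before, so readers will tend to take the curve as the regimen's risk. The same section of the report would then give two different percentages for what looks like one quantity, and the difference grows with follow-up.

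**Working it through.** The protocol gives no toxicity rate for this analysis, so there is no planned figure to reproduce. The check covers direction and size.

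**Inputs from the protocol.** Section 11.4: "A PFS of 3 months is not considered of interest. A PFS of 6 months is expected", restated as "a PFS of 50% at 3 months is insufficient and a PFS of 70.7% is expected". Read as medians with exponential times, 0.5^(3/6) = 0.707 and 0.5^(3/3) = 0.50, so the two statements agree. The exit rate at the expected PFS is ln2/6 = 0.1155 per month. Section 1 gives a median OS of around 30 months in recent trials, so the death rate is ln2/30 = 0.0231 per month. The sample size is 57.

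**Assumed inputs.** Monthly hazard of first grade 3-4 toxicity, in four versions: 0.15 or 0.25 for 3 months then 0.03 (most toxicity early), and constant 0.05 or 0.10.

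**Formulas.** With toxicity hazard h, cumulative toxicity hazard H and cumulative exit hazard C:

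- 1 − KM(t) = 1 − exp(−H(t))
- cumulative incidence(t) = ∫₀ᵗ h(u) exp(−H(u) − C(u)) du

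**One case in full** (0.15 then 0.03; exits at 0.1155 starting at month 3):

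- Month 6: H = 0.45 + 0.09 = 0.54, so 1 − KM = 41.7%. Cumulative incidence = (1 − e^−0.45) + e^−0.45 × 0.03/0.1455 × (1 − e^(−0.1455×3)) = 0.362 + 0.047 = 40.9%. Gap 0.8 points.
- Month 12: H = 0.72, so 1 − KM = 51.3%. Cumulative incidence = 0.362 + 0.638 × 0.206 × (1 − e^(−0.1455×9)) = 45.8%. Gap 5.5 points.

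**All cases** (gap = 1 − KM minus cumulative incidence, in points):

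| Toxicity hazard per month | 1 − KM, month 6 / 12 | Exits from month 3: gap month 6 / 12 | Death only: gap month 6 / 12 | Everyone exits at progression, from day 0: gap month 6 / 12 |
|---|---|---|---|---|
| 0.15, then 0.03 | 41.7% / 51.3% | 0.8 / 5.5 | 1.7 / 3.5 | 7.4 / 13.5 |
| 0.25, then 0.03 | 56.8% / 63.9% | 0.6 / 4.1 | 2.0 / 3.3 | 8.8 / 13.4 |
| 0.05 constant | 25.9% / 45.1% | 1.8 / 11.1 | 1.6 / 5.2 | 6.9 / 19.1 |
| 0.10 constant | 45.1% / 69.9% | 2.8 / 14.5 | 2.7 / 7.2 | 11.5 / 27.0 |

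Exits from month 3 are a reasonable middle case. The first on-treatment CT is at Cycle 6, about month 3, and recording can run 90 days past the last dose. The last column is an upper bound at the 6-month median, because it closes observation at progression.

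**Against sampling error.** The Greenwood standard error of the month-12 Kaplan-Meier estimate with 57 patients is 7.2 to 8.5 points in the middle case. The gap is therefore about 0.6 (4.1/7.2) to 1.8 (14.5/8.1) standard errors.

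**The crude percentage.** In simulated trials of 57 with constant hazards, a 50% risk by month 6 in the absence of exits, and exits at a 6-month median, the mean month-6 estimates were 50.2% by Kaplan-Meier, 37.8% by Aalen-Johansen and 37.8% as the crude proportion. The crude figure does not carry the inflation.

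**The case against.** The strongest defence has four parts.

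1. **The unaffected number is already planned.** The list reports the number and percentage with a grade 3 or 4 event, and the Kaplan-Meier line can be read as describing timing only. This stands in part. A reader might infer that the trial's reported toxicity rate is overstated, and the protocol does not support that: only the curve is affected. A Kaplan-Meier curve is nevertheless commonly read as a probability, and nothing in Section 11.3.1 warns against it.
2. **No decision uses the curve.** The Step 1 rule (Sections 11.3 and 11.3.4) counts patients with the same grade 3-4 event in the first two cycles. This stands fully. It would be wrong to infer that the Step 1 primary safety conclusion is at risk.
3. **Progression does not end observation.** A reader might take every progression to be a censoring. Sections 9, 5.2.2 and 10.2.1 let treatment, retreatment and AE recording go on after it. FOLFOX is scheduled only to V6 and tremelimumab to V7, so exposure to the full combination is early. This stands, and it is why the exit-at-progression column is only an upper bound.
4. **The direction is not fixed in every respect.** If exits are independent of toxicity, one minus Kaplan-Meier validly estimates the risk while under observation. A fatal toxicity with no earlier grade 3-4 event would be censored as worded, which pulls the curve down. Both statements are true. The protocol does not say it wants the first quantity, and the second is a further reason to reword the sentence.

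An unseen statistical analysis plan could settle censoring dates. It would not undo an estimator and a blanket censoring rule that the protocol already states.

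**Conclusion.** The point holds for the Kaplan-Meier curve read as an absolute risk. Deaths and closures of recording at new therapy are censored, so the curve lies above the proportion of treated patients with grade 3-4 toxicity, and the difference widens with time.

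Under the assumed hazards and a 6-month median PFS, the plausible size is small at month 6 and possibly material by month 12: the middle column of the table, with death alone giving less at month 12. All sizes rest on assumed toxicity hazards, exponential exits and the reading of PFS as an exit rate. If median PFS were nearer the 3 months that the protocol regards as uninteresting, exits would be faster and the gaps larger.

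This is a worthwhile correction to a descriptive safety summary. It does not affect the Step 1 stopping rule, the crude toxicity percentage or the efficacy conclusion.

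**What to change.** Replace the Kaplan-Meier and censoring sentences in Section 11.3.1 with:

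*Cumulative incidence of first grade 3 or higher toxicity will be estimated by the Aalen-Johansen method, with death without prior grade 3 or higher toxicity and start of another anticancer therapy as competing events. Patients still under AE observation at data cut-off, lost to follow-up, or reaching the end of the 90-day recording window are censored.*

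Add that progression alone is neither a competing nor a censoring event, so that toxicity in patients treated or retreated after progression still counts. Wording the event as grade 3 or higher keeps a fatal toxicity in the numerator. Keep the crude number and percentage beside it.

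The cost is one sentence and a slightly less familiar estimator. No new data are needed: death dates are collected for OS, and the start of another therapy already closes AE recording under Section 10.2.1.

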### **11.3.2. Efficacy Analyses set**

Efficacy analyses will be performed in modified intent-to-treat population (ITT) population ie, all patients following the major inclusion criteria and with a 3 months evaluation. Analyses will be repeated in the intent to treat principle i.e including all enrolled patients whatever eligibility criteria and treatment received patients and in the per protocol population (patients who had received all the planned doses).

The primary objective will be evaluated at 3 months among MSS patients only. According to the Simon's design, at 3 months, on the first evaluable 43 patients (mITT population): if 26 or more patients respond to treatment the treatment will be considered of interest for evaluation in a phase III trial. Response rates will be evaluated using RECIST criteria. Response will be considered for patient with Complet response (CR), partial response (PR) and stable disease (SD). Overall survival and progression free survival (OS and PFS) will be estimated using Kaplan Meier method. Median survivals will be reported with 95% confidence intervals (CI).

Median follow-up will be estimated using the reverse Kaplan Meier method.

Analysis of survival and response among MSI patients will be performed in an exploratory manner, taken into account the small sample size in this population. All statistical analysis will be performed with Stata 11 or SAS 9.3.

### **11.3.3. Exploratory Analyses**

Analysis of immunogenicity will be done as the standard practice used at the "plateforme de transfert en biologie cancérologie" (PTBC) from Dijon.

### **11.3.4. Interim analyses**

2 interims analyses are planned: after the inclusion of 9 patients for the step 1 safety analysis and after 16 patients for step 2 of efficacy analysis (Simon's design).

**STEP 1:** An interim analysis is plan after the inclusion of the patient 9 from step with at least two cycles of treatment performed. The purpose of this interim analysis is to stop the study if a to high numbers of toxicity is observed. If the same grade 3-4 adverse event is reported during the first 2 cycles for more than 3 patients over 9, the trial could prematurely be stopped. The independent data monitoring committee will also meet in order to analysis all the toxicity observed on the 9 first patient with a minimum of 2 cycles of traitement.

**STEP2:** The efficacy of the treatment scheme will be determined in a 2-step phase II study. A second interim analysis will be performed after 16 subjects evaluable for the primary objective (3 months evaluation). On these 16 first evaluable subjects, if 9 or more are in response to treatment, the study will continue and the additional 27 subjects could be enrolled. If 8 or less subjects are in response, the study could be stopped because of futility, after decision of the independent committee. The study can't stop in favor of efficacy. Inclusions will not be stop during this interim analysis in order to maintain the enrollment dynamic.

#### **11.4. Determination of sample size**

**Step 1:** Nine patients will be included in the **safety** analyses. If the same grade 3-4 adverse event is reported for more than 1 patient over 3, the trial could prematurely stop after reunion of the independent committee. Patients from the safety population will be included in the efficacy set.

**Step 2:** The **efficacy** will be determined using a Simon 2 steps phase II design.

The hypotheses are the following:

The primary objective will be evaluated among MSS patients

A PFS of 3 months is not considered of interest. A PFS of 6 months is expected. This is equivalent to assume that a PFS of 50% at 3 months is insufficient and a PFS of 70.7% is expected. With  $\alpha=10\%$ ,  $\beta=10\%$  (90% power), 20% of non-evaluable patients, 52 patients with MSS disease are needed including patients of the safety population (9 patients)

The prevalence of MSS disease is around 90%-95%, thus 5 additional patients will be included

Overall the study will include 57 patients.

## **12. ETHICAL AND REGULATORY REQUIREMENTS**

### **12.1. Ethical conduct of the study**

The study will be performed in accordance with ethical principles that have their origin in the Declaration of Helsinki and are consistent with ICH/Good Clinical Practice, and applicable regulatory requirements Subject data protection.

## **12.2. Ethics and regulatory review**

Before carrying out biomedical research on humans, the sponsor is required to submit the project to the opinion of one of the competent institutional review board where the coordinating investigator operates.

The request of an opinion of the biomedical research project is sent to the committee by the sponsor.

Applications for substantial modifications of the initial projects are also addressed by the sponsor for an opinion from the committee.

## **12.3. Informed consent**

Prior to the implementation of the biomedical research on a person, subject should be fully informed by the investigator during the consultation and after a period of reflection sufficient written informed consent form should be collected.

The information for the trial participants should include all elements defined in the Public Health Act of August 9, 2004 and must be written in a simple and understandable language for the patient.

The consent form must be dated and signed personally by the research participant and investigator (original archived by the investigator, a copy will be given to the research participant).

In the case of research aimed to carry out analyzes of genomics or proteomics, the informed consent form should specify the type of research to be conducted and the patient must have the ability to accept or decline conservation of biological samples for a scientific research purposes.

